### 2.2. Statistical Analysis

Primary statistical modeling will be performed based on the change in outcomes from baseline to 6-months post-intervention between the two randomized groups. Descriptive analysis of all data collected, using typical graphic and numerical exploratory data techniques, is planned. An intention to treat approach will be used to avoid bias from noncompliance and missing outcomes for primary analyses of the treatment effect between two groups. Regression models will be used for modeling treatment effects while adjusting other covariates. Post hoc multiple comparisons tests are applied to adjust for pairwise comparisons.

#### Sample Size and Interim Analysis

The primary objective is to compare the change in BMI in the two groups from pre-intervention to post-intervention after six months (intervention completion). The analysis for this primary objective will be based on the multivariate linear regression with adjustment for potential confounders. The difference for the change of BMI between the two groups will be estimated, and a corresponding 95 percent confidence interval will be calculated.

The sample size of the FIREHOUSE trial was estimated by the power analysis for the primary outcome of the change in BMI predicted between the start and end of the intervention, which was based on a two-sample test to compare the outcome between two groups under 1:1 randomization. According to the preliminary data, we assumed SD = 2 kg/m^2^ and the means of two groups “Usual Care” and “LoCalMed” to be 0 and −1 kg/m^2^, respectively. Furthermore, 6-month interventions with similar calorie targets and behavioral modification with exercise produce a 7–10 percent weight loss [37,38]. A total sample of 128 subjects (64 subjects in each arm) can achieve 80 percent power at α = 0.05. We will recruit 140 subjects accounting for potential loss of around 20 percent drop out.

The interim analysis plan will incorporate two interim looks and one final look, with all looks named as formal interim analysis, Table 5. This study will not be monitored for futility. The first look will be conducted at the completion of 6-month intervention or observation for 30 subjects in each group. This look will use 2-sided α < 0.001. The second look will be one formal interim look, which will be conducted at the completion of 50 subjects in each group with a 2-sided α = 0.007. The final analysis will take place at completion of all subjects in each group, with an O’Brien Fleming boundary for a 3-look design with 2-sided α = 0.033, Table 5 and Figure S1.

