**Exploratory Endpoints**	Microbiome	GenoTek Oragene-Gut personal stool collection kit
	Genome	DNA GenoTek Oragene-Discover saliva collection kit

FEV_1_, forced expiratory volume in one second; ATS/ERS, American Thoracic Society/European Respiratory Society; BIA, bio-electrical impedance analysis; BMI, body mass index; FeNO, fractionated exhaled nitrous oxide; ECG, electrocardiogram; BP, blood pressure; HR, heart rate; RR, respiratory rate. Table 4 details the primary, secondary, and exploratory endpoints of the study. Along with each endpoint is a description of what that measurement consists of.

**Table 5 ijerph-17-06569-t005:** Interim Monitoring Bounds.

Interim Analysis	Completion of Subjects/Group	Critical Value Z ±	*p* Value
1	30	3.951	0.000
2	50	2.686	0.007
3	70	2.129	0.033

Interpolated boundaries with 3-look O’Brien Fleming stopping boundaries 140 subjects randomized with 2-sided α = 0.036, power = 80%. Table 5 describes the statistical measures which will be the basis for our interim analysis.

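### Sample size is set at α = 0.05 with a single fixed test, but Table 5 judges the primary comparison at an overall α of 0.036, so 128 completers give about 76% power, not 80%

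*Protocol article*

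**What the plan says.** Three statements in the protocol article bear on the level and power of the primary BMI comparison.

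- **Sample size** (Sample Size and Interim Analysis). The calculation is "based on a two-sample test to compare the outcome between two groups under 1:1 randomization". It assumes an SD of 2 kg/m² and "the means of two groups “Usual Care” and “LoCalMed” to be 0 and −1 kg/m^2^, respectively". It concludes: "A total sample of 128 subjects (64 subjects in each arm) can achieve 80 percent power at α = 0.05". Then: "We will recruit 140 subjects accounting for potential loss of around 20 percent drop out".
- **Interim plan** (same section). The first look comes at "completion of 6-month intervention or observation for 30 subjects in each group", with a two-sided level below 0.001. The second comes at 50 per group with 0.007. The final look is described as an O'Brien-Fleming "boundary for a 3-look design with 2-sided α = 0.033, Table 5 and Figure S1". There is no futility monitoring. The same section plans a 95% confidence interval for the difference.
- **Table 5.** The critical values are 3.951, 2.686 and 2.129 at 30, 50 and 70 per group. The footnote describes "140 subjects randomized with 2-sided α = 0.036, power = 80" percent.

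**The concern.** Three levels (0.05, 0.036 and 0.033) are attached to one primary comparison, and the text does not say how they relate. The sample size uses 0.05 and a single test. The decision rule uses 0.036 and three looks. The section's wording makes 0.033 look like the level of the whole three-look design, whereas in Table 5 it is the nominal level of the last look. Table 4 lists a single primary endpoint, and nothing in the document reserves the gap between 0.036 and 0.05 for another test.

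Two things are at stake. First, a reader will take 80% as the power of this trial with 128 completers, and under the rule that will be applied it is lower. Second, the decision threshold is ambiguous: a final p value between 0.033 and 0.05 would give an unadjusted 95% interval that excludes zero beside a primary test that has not crossed its bound.

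**Working it through.** **Inputs.** Difference δ = 1, SD σ = 2, 1:1 allocation, 64 or 70 per arm, α = 0.05 (Sample Size and Interim Analysis); bounds 3.951, 2.686, 2.129 at 30, 50, 70 per group and overall α = 0.036 (Table 5).

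**1. The plan's own figure.** For a fixed two-sample t test the noncentrality is δ / (σ√(2/n)). At n = 64 this is 1 / (2 × √(2/64)) = 2.828. Power at two-sided 0.05 is 80.1% (79.5% at 63 per arm). So 64 per arm is correct for a single test at 0.05.

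**2. Level of the Table 5 bounds.** The two-sided nominal p values of the three bounds are 0.00008, 0.0072 and 0.0333, which match the table. Numerical recursive integration over looks at 30, 50 and 70 per group, under no effect, gives:

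| Look | Cumulative two-sided type I error |
|---|---|
| 1 | 0.0001 |
| 2 | 0.0072 |
| 3 | 0.0351 |

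With equally spaced looks the total would be 0.0355. The label 0.036 is therefore about right, and 0.05 − 0.035 = 0.015 is not spent.

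**3. Power under the Table 5 bounds.** Same recursion, δ = 1, with looks at 30, 50 and the final number per arm:

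| Completers per arm | Total | Power |
|---|---|---|
| 64 | 128 | 76.0% |
| 70 | 140 | 79.9% |
| 71 | 142 | 80.5% |

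A hand check uses the final look alone. At 64 per arm, Φ(2.828 − 2.129) = Φ(0.699) = 0.758. At 70 per arm the drift is 1 / (2 × √(2/70)) = 2.958, and Φ(2.958 − 2.129) = Φ(0.829) = 0.796. The earlier looks add only a few tenths of a point.

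**4. What 140 stands for.** The footnote's 80% needs 140 analysed subjects, but the sample-size text recruits 140 to absorb around 20% loss. At that loss 140 × 0.8 = 112 remain (56 per arm), and power under the Table 5 bounds is 69.8%. Part of that fall is a separate matter: going from 140 to 128 allows only 1 − 128/140 = 8.6% loss. The shortfall at 128 completers (80.1% against 76.0%) holds whatever the drop-out.

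**5. Do three looks require 0.036?** No. Keeping the printed bounds at looks 1 and 2 and spending the rest of 0.05 at 70 per arm gives a final Z of 1.971 (nominal p 0.049). Power is then 84.0% at 70 per arm and 80.6% at 64 per arm. The smallest significant final difference at 70 per arm, Z × 2 × √(2/70), moves from 2.129 × 0.338 = 0.72 to 1.971 × 0.338 = 0.67 kg/m².

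**The case against.** The best defence is that each statement is right on its own terms. The sample-size sentence refers to a two-sample test and reproduces. The Table 5 footnote refers to the sequential design with 140 subjects and also reproduces (79.9%). Bounds that spend less than 0.05 cannot produce excess false positives, no rule obliges a trial to spend all of 0.05, and the protocol calls the trial exploratory. All of this stands. It makes the problem one of two unreconciled statements and lost power, not of faulty arithmetic or an invalid test. It does not remove the problem, because only one of the two tests will be run and the same 140 cannot be both the number analysed and the number that allows for loss.

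Two stronger readings are tempting.

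- A reader might infer that 0.036 was solved backwards from 140 subjects and 80% power, since a fixed t test with 70 per arm has 80% power at α = 0.0364. The match shows only that the footnote's figures agree with each other. The document does not say how 0.036 was chosen, and the reason may lie in the full protocol or Figure S1, neither of which is shown.
- A reader might conclude that all three bounds should be replaced by O'Brien-Fleming-type spending of 0.05 (Z = 3.23, 2.42, 2.00). At look 1 that gives p = 0.0012, against the plan's own rule of below 0.001. Under the assumed effect it also raises the chance of crossing at look 1 from 2.2% to 9.8%, and by look 2 from 42.6% to 53.4%. The trial is un-blinded and under way, so the conflict in the text does not justify loosening the early looks.

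**Conclusion.** The concern holds as an inconsistency with a modest but real cost. The sample size rests on one α and one test; the decision rests on another α and a sequential test; no reason is given. Under the rule to be applied, 128 completers give about 76% power, some 4 points below the stated 80%, and 80% is reached only if essentially all 140 recruited subjects complete. Type I error stays at about 0.035, so no false-positive risk follows.

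The figures assume the plan's own difference and SD, a normal test statistic, no covariate gain and the first two looks at 30 and 50 per group. Baseline adjustment in the planned regression could raise power, but the sizing does not count on it and gives no figure from which to estimate the gain. This calls for reconciling the text. It does not put the validity of the primary test in doubt.

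**What to change.** State one overall two-sided α for the primary comparison, and align the sample-size sentence, Table 5 and the confidence level with it.

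- **If 0.036 is kept:** replace 0.05 in the sample-size sentence. Give power as about 76% for 128 completers and about 80% only for 140 completers. Call 0.033 the nominal level of the final look, not the level of the three-look design. Make the interval's confidence level consistent with that rule. This changes wording only.
- **If 0.05 is intended, and no unblinded comparison has yet been made:** leave the printed bounds at looks 1 and 2 and recompute only the final one (Z about 1.97, nominal p about 0.049). Power is then about 84% at 70 per arm, the early looks are unchanged and the look 1 rule of p below 0.001 is respected. The cost is one row of Table 5 and its footnote, the matching final-look sentence and a dated record of the change. No extra subjects are needed.

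The document does not say whether the look at 30 per group has taken place. If it has, only the first option is open. Under either option, say whether 140 is the number recruited or the number analysed.

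### Recruiting 140 does not cover the stated 20 percent drop-out: 128 completers would need 160, and power under the plan's own loss assumption is about 75 percent, or about 70 percent with Table 5's bounds

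*Protocol article*

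**What the plan says.** All the figures are in the protocol article, section 2.2, under Sample Size and Interim Analysis, and in Table 5.

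- **Method:** the calculation is "based on a two-sample test to compare the outcome between two groups under 1:1 randomization".
- **Inputs:** "we assumed SD = 2 kg/m^2^ and the means of two groups" for Usual Care and LoCalMed "to be 0 and −1 kg/m^2^, respectively".
- **Required number:** "A total sample of 128 subjects (64 subjects in each arm) can achieve 80 percent power at α = 0.05".
- **Recruitment:** "We will recruit 140 subjects accounting for potential loss of around 20 percent drop out".
- **Monitoring design:** the Table 5 footnote gives "140 subjects randomized with 2-sided α = 0.036, power = 80" percent. The table's final look is at 70 completed subjects per group, with critical values 3.951, 2.686 and 2.129 at 30, 50 and 70 per group.

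**The concern.** The 128 is a number of subjects with an observed outcome. A recruitment target that allows for 20% loss must leave 128 after that loss, and 140 plainly does not. The 12 subjects above 128 are under a tenth of the recruits.

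Table 5 adds a second conflict. It claims 80% power for 140 subjects at a stricter overall alpha (0.036 rather than 0.05), and it counts all 70 per group as completers. So the same 12 subjects are used twice: in the text as the drop-out allowance, and in Table 5 to pay for the stricter sequential alpha.

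What is at stake is how a null primary result is read. Readers would take it as coming from a trial with a 20% chance of missing a 1 kg/m² difference, when the plan's own assumptions imply a larger chance.

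**Working it through.** **Inputs** (Sample Size and Interim Analysis; Table 5): difference δ = 0 − (−1) = 1 kg/m²; SD σ = 2 kg/m²; 1:1 allocation; alpha 0.05, taken as two-sided because the monitoring plan is two-sided and a one-sided test would need only 50 per arm; 140 recruited; 20% loss.

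**1. Reproduce the 128.** For a two-sample t-test with n per arm, the noncentrality is δ / (σ√(2/n)) on 2n − 2 degrees of freedom.

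- n = 63: power 79.5%
- n = 64: noncentrality 1 / (2 × √(2/64)) = 2.83, power 80.1%

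So 64 per arm, 128 in total, is correct.

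**2. Apply the stated drop-out.**

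- Recruits needed: 128 / (1 − 0.20) = 160, or 80 per arm.
- The common shortcut 128 × 1.20 = 153.6, rounded up to 154, also exceeds 140.
- Completers from 140: 140 × 0.80 = 112, or 56 per arm.
- Loss that 140 can absorb: 1 − 128/140 = 8.6%.

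**3. Power at fixed two-sided alpha 0.05, with 140 recruited.**

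| Loss | Completers | Power (t-test) |
|---|---|---|
| 5% | 133 | 81.6% |
| 8.6% | 128 | 80.1% |
| 10% | 126 | 79.5% |
| 15% | 119 | 77.2% |
| 20% | 112 | 74.6% |

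At 56 per arm the noncentrality is 1 / (2 × √(2/56)) = 2.65. The normal approximation gives 75.4% there.

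**4. Power with the Table 5 bounds.** At n per group the information is n/(2σ²). The score statistic is normal with mean δ × information and variance equal to the information, with independent increments. The null is rejected if |Z| exceeds 3.951 at 30, 2.686 at 50, or 2.129 at the final n. Numerical integration gives:

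| Final n per group | Overall alpha | Power |
|---|---|---|
| 70 (no loss) | 0.035 | 79.9% |
| 64 | 0.034 | 76.0% |
| 56 (20% loss) | 0.034 | 69.8% |

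The first row matches the footnote's 80%, which confirms that Table 5 assumes no drop-out. The last two rows hold the final critical value at 2.129 when the last look falls at a smaller n.

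**The case against.** The arithmetic is not in dispute. The objections concern how far it reaches.

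- **The shortfall depends on the loss rate.** The Discussion reports recall of at least 90% in earlier studies. At 10% loss, power is 79.5% at alpha 0.05, close to target. This stands: the deficit exists under the plan's own 20%, not at every rate. But then the 20% is the wrong figure in the text, and even with 64 completers per group Table 5's bounds give only 76.0%.
- **The 70% combines two effects.** Drop-out alone costs about 5 points. The rest comes mainly from Table 5's tighter alpha, and assumes that its final bound is not recomputed. With the interim bounds kept and the final bound relaxed to 1.99, overall alpha stays below 0.05 and power at 56 per group is about 74.4%. This is fair, and is why the two figures should be reported separately.
- **Covariate adjustment may help.** The primary analysis is an adjusted regression. At 56 per arm, 80% returns if the residual SD is about 1.87, that is, if covariates explain about 1 − (1.87/2)² = 13% of the variance. The article claims no such gain, and the stated calculation is unadjusted.
- **The effect may be larger, and the trial is called exploratory.** The target is a BMI change of 1 to 2 units. At a difference of 1.5, 56 per arm gives 97.6%. But the stated power is for a difference of 1, and the trial has formal stopping bounds and an explicit power claim.

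Intention to treat does not answer the point, because it does not restore the information lost with missing 6-month BMI.

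**Conclusion.** The concern holds. The 128 is right, but the statement that 140 covers around 20% drop-out is wrong by 20 subjects. Under that drop-out rate, power for the planned difference is 74.6% at fixed alpha 0.05 and 69.8% with Table 5 as written, so the type II risk is about 25 to 30% instead of 20%.

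This rests on the plan's own difference and SD, equal loss in both arms, an unadjusted comparison of completers and, for the Table 5 figure, unchanged critical values. The error does not bias the treatment estimate. It makes the stated power of the primary analysis incorrect and leaves the text and Table 5 inconsistent.

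**What to change.** Keep 140 and restate the figures in one of two ways.

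- **(a) Restate the tolerated loss:** say that 140 allows for about 9% loss at fixed alpha 0.05. This should rest on evidence that such retention is realistic here. The recall figure in the Discussion is close to it, but section 2.3 reports that the pandemic pause affected final visits.
- **(b) Restate the power:** keep 20% loss and give power of about 75% at fixed alpha 0.05, or about 70% with the Table 5 bounds.

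In either case, delete the claim that 140 covers 20%, and base the power in the Table 5 footnote on the expected number of completers, not on 70 per group.

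The cost is one or two sentences and a table footnote, with no extra subjects. Under (b), and in Table 5, the stated power becomes less favourable. If the sponsor wants 80% at fixed alpha 0.05 with 20% loss, the alternative is to recruit 160, which is 20 more subjects. That would still give only 76.0% at 64 completers per group under Table 5's bounds.

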### 2.3. COVID-19 Pandemic Precautions

Coronavirus disease 2019 (COVID-19), caused by the severe acute respiratory syndrome coronavirus 2 (SARS-CoV-2), emerged in Wuhan, China, in late 2019 and has since developed into a pandemic. During the FIREHOUSE RCT’s enrollment period, New York State emerged as an epicenter of the global health emergency [39,40,41,42,43,44,45,46,47,48,49].

In response to this novel respiratory pathogen, NYU paused face-to-face clinical research for many studies in order to assess, address and minimize any potential COVID-19-related risks. This impacted our in-person baseline visits as well as final study visits. Meetings with our nutritionist continued for subjects already enrolled since these were designed to be on a video platform.

Once safe to resume these activities, we implemented a COVID-19 pre-visit screening with subjects. This “Research Participant Information Sheet: COVID-19 Updates” informs both newly screened/enrolled subjects as well as subjects returning for their follow-up evaluation about the safeguards that have been put into place to protect against the risk of COVID-19 transmission while restarting certain in-person research activities.

Specifically, subjects were informed that since some study visits need to be conducted in person, participation in these study activities may increase their risk of exposure to the COVID-19 virus. We also discussed that NYU, as with nearly all public venues, has implemented a number of safety policies to protect subjects and to reduce exposure risk. These policies include, among other requirements, screening all persons involved in research visits (staff and study subjects), use of Personal Protective Equipment (PPE), following Social Distancing guidelines when possible, and cleaning and sanitizing rooms and equipment. These protective measures are similar to those most doctors’ offices have implemented in response to COVID-19.

This participant information document also informs subjects that their participation is completely voluntary. Additionally, subjects are provided with the Principal Investigator (PI)’s contact information and given the opportunity to ask any questions that may arise. A copy of this information sheet is also provided to the patient.

Due to the pause, the final study visit timeframe, to the extent to which it could be performed, was extended for at least three additional months. Since spirometry and FeNO assessment may lead to aerosolization, we also suspended their assessment for the purposes of research during the COVID-19 pandemic.

## 3. Discussion

The impact on quality of life and financial burden of WTC-LI are public health concerns. Despite treatment, new cases continue to be identified, and those affected continue to experience morbidity. Our work fits into broader literature that explores the association of poor metabolic health and OAD in those exposed to pollution. Although the mechanisms that lead to lung disease in the context of pollution and metabolic syndrome remain poorly understood, we have shown that modifiable risks such as BMI and dyslipidemia can predict development of WTC-LI. In the FIREHOUSE RCT, we will investigate dietary intervention as a treatment of WTC-LI.

Our prior investigations, from which the FIREHOUSE RCT stems, allowed us to discover and validate a metabolomic signature of WTC-LI, while investigating the effects of confounders found in the entire FDNY cohort such as smoking, obesity, and diet. Since dietary habits have a direct relationship to MetSyn and the metabolome, we propose to alter the subjects’ nutritional status using a Mediterranean style diet.

Our current WTC portfolio lacks insight into dietary patterns and quality of life measures as they pertain to metabolic risk. Furthermore, it lacks direct vascular injury measures and assessments of FeNO and PWV. In the context of our preliminary findings, and due to a clinical need, we propose an RCT to assess the effect of dietary modification on BMI, lung function, vascular injury, and quality of life measures. We measure PWV, a marker of central aortic stiffness, which has implications in cardiovascular disease [50,51,52,53,54]. A meta-analysis of 20 studies showed that modest weight loss (eight percent of the initial body weight) caused a reduction in PWV measured in all arterial segments [55,56]. A systematic review and meta-analysis of RCTs looking at the effect of dietary interventions found that polyunsaturated fatty acids (PUFA) supplementation improved PWV [57,58]. Pulmonary vascular injury occurs early in obstruction, prior to the development of abnormal FEV_1_ [59,60]. We have published that enlarged pulmonary artery/aorta ratio by CT scan and dyslipidemia are biomarkers of WTC-LI [61]. FeNO, a clinically accepted, indirect biomarker of lung disease activity, will be a valuable measure in our population. FeNO is associated with airway hyperreactivity, and several studies show that FeNO increases during obstructive exacerbations [62].

We propose to sample, bank, and measure serum and plasma for biomarker assessment before and after the dietary intervention. Biomarkers are powerful predictors of disease that are useful in defining the efficacy of our intervention. This biorepository will not only allow us to complete and evaluate our current clinical trial but will be valuable to future epigenetic studies of WTC disease. Assaying biologically relevant biomarkers allows for the identification of relevant pathways involved in WTC-LI and helps guide therapies targeting these mediators. We will also obtain peripheral blood mononuclear cells from collected blood that will allow us to assess the genomic and microbiomic signatures pre/post intervention.

There are limitations to this study, and a few will be discussed in this protocol paper. First, the study population is male and largely Caucasian, which may limit generalizability. To limit bias in this un-blinded study, we will randomize after visit one. However, there is a chance that the main research team (not including the nutritionist and technology support providers) will be privy to subject identities and experimenter bias. Given the tightly knit nature of the FDNY community, we also surmise that there could be some sharing of information regarding the protocol between participants in opposing treatment arms. Furthermore, as a behavioral and educational intervention, there is marked variability among individuals with regard to technologic savviness, educational background, willingness to alter diet and exercise, social support, economic means for a healthier diet, and physical ability to exercise. This variability will be equally prevalent in both groups. Similarly, subjects unwilling to participate fully will not pass the inclusion criteria.

The FDNY cohort is highly motivated to improve their disease burden and quality of life. Rescue workers receive routine screening and have an excellent recall of at least 90 percent in prior clinical studies. In addition, there is a strong commitment at the FDNY for this proposed collaborative NYU/FDNY effort to improve the health of these brave individuals. Many participants are aware of our previous findings and have asked for ways to modify their lifestyle with hopes of changing disease outcomes. Hence, it is logical to provide this much-affected cohort with interventions that they may benefit from. This intervention, once validated, may yield meaningful findings for populations exposed to ambient and other occupational particulates.

